**Methods:**

A pilot randomised controlled trial feasibility study will be implemented. A group receiving the SOLACE stigma support intervention (*n* = 12) will be compared against a control group not receiving any additional intervention (*n* = 12). Family carers of autistic children up to the age of 10, who have been recently diagnosed or are currently undergoing diagnosis, will be recruited for the study. Participants will be randomly allocated to the intervention or control group and will take part in eight weekly group-based sessions designed to improve the well-being of the parents primarily through increasing their resilience to stigma. Feasibility will be determined by recruitment and retention rates and a qualitative focus group evaluating the acceptability of the intervention and outcome measures. The primary outcome of interest is psychological well-being, and depending on the normality of distribution, independent samples *T* tests will be used to compare the outcome scores between the two groups and dependent samples *T* tests for differences within the group. Other outcomes of interest are stigma, self-stigma, self-esteem, self-blame, social isolation, self-compassion and perceived responsibility and control.

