## Methods

### Design

This study is a feasibility study of a parallel randomised controlled trial (RCT) that compares changes in outcomes of interest among parents/carers allocated to the SOLACE experimental group against parents/carers allocated to a control group (no intervention). Standard Protocol Items: Recommendations for Interventional Trials (SPIRIT) checklist was used to structure and develop this protocol.

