### Randomisation and blinding

After completing the baseline questionnaire, all participants eligible to take part will be stratified based on gender and frequency of use of support groups (ranging from 0 (never) to 4 (often)) to minimise imbalance between the two groups. The participants will be randomised by an independent researcher via computer generated allocation using JavaScript’s Math functions [33] to either the SOLACE intervention or to the control group. Double-blinding of group allocation is not practically possible since the intervention will be facilitated by the researchers. Figure S1 illustrates the recruitment process and can be found in Additional file 1.

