### Statistical analysis

Statistical analysis (using IBM SPSS v23 software) of the quantitative outcome measurements will be conducted following tool analytical guidance. Within group comparisons of the outcomes, measures will be made as well as between groups comparisons to examine preliminary effectiveness.

Kolmogorov–Smirnov tests will be initially conducted to establish the normality of the data. Depending on the normality of distribution, independent samples *T* tests, Mann–Whitney *U* tests and/or chi-square tests will be used to compare the outcome measures between the two groups. To assess potential within-group differences, dependent *T* tests (for normal distribution) or Wilcoxon signed-rank tests (for non-normal distribution) will be used. Individual and group-level descriptive analyses of both the frequency and/or central distribution (medians, means, standard deviation, range) of independent and dependent variables will also be conducted. Standard effect sizes of the primary outcome measure will be calculated (Cohen’s *α*) with confidence intervals to provide an initial estimate for sample size calculation for a future main RCT.

Furthermore, quantitative data will be descriptively analysed to assess rates and patterns of recruitment, follow-up and retention rates, and willingness of randomisation. The distribution of missing data within each measure will help to establish the acceptability of measures. Missing data will also be described via frequencies and cross tabulations against background characteristics to further assess the acceptability of the measurement tools.

Qualitative data will be thematically analysed using Nvivo (v11). This will involve in-depth familiarisation with the focus group data, systematic identification of codes to form a coding frame, indexing the data according to the coding frame to identify common themes and interpreting the findings in the context of other research [47].

The Consolidated Standard of Reporting Trials (CONSORT) extension to pilot trials will be followed for reporting the trial.

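### The between-group comparison is fixed as unadjusted two-sample tests, on scores in one section and changes in another, with no adjustment for the baseline value the trial already collects

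*Protocol article*

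**What the plan says.** The Statistical analysis section names the between-group methods. After a normality check, independent samples t tests, Mann-Whitney U tests and/or "chi-square tests will be used to compare the outcome measures between the two groups". It mentions no covariate, regression model or stratum term. The baseline value clearly enters only the paired tests within each arm ("To assess potential within-group differences, dependent" t tests or Wilcoxon signed-rank tests).

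Two other places describe the quantity compared, and they differ. In the Abstract (Methods), t "tests will be used to compare the outcome scores between the two groups". The Design section says the trial "compares changes in outcomes of interest among parents/carers allocated to the SOLACE experimental group" with the control group. The Statistical analysis section speaks only of outcome measures, which fits either.

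Randomisation and blinding puts the baseline questionnaire before allocation ("After completing the baseline questionnaire, all participants eligible to take part will be stratified"). Participants are "stratified based on gender and frequency of use of support groups", the latter scored 0 to 4, and the stated purpose is "to minimise imbalance between the two groups".

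The Statistical analysis section then sends the standardised effect size of the primary outcome measure, with its confidence interval, to the main-trial sample size calculation. The Discussion expects that indication to be reliable.

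**The concern.** The design takes trouble over imbalance at allocation, and the analysis then makes no use of the one variable likely to matter most, the participant's own starting score. In a trial of 24 people the arms can easily start some way apart on MHI-5. An unadjusted follow-up comparison carries part of that gap into the estimated effect.

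No confirmatory test is at stake. What suffers is the effect size and interval passed to the next trial, which are noisier than they need be whenever baseline predicts follow-up. The mismatch between scores and changes adds a second problem. The two analyses have different precision, and a standardised effect divided by the SD of change is a different number from one divided by the SD of scores. A later sample size calculation could take up either without knowing which.

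**Working it through.** **Inputs.** 12 per arm, 24 in all (Sample size section), all analysed. Outcomes are in SD units, with the same SD at baseline and follow-up. The baseline/follow-up correlation *r* is not in the documents, so it is assumed over a range. The target of 24 has no power calculation behind it, so there is no figure of the plan's own to reproduce.

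**Chance baseline imbalance.** The SD of the difference in baseline means is √(2/12) = 0.408. The probability that it exceeds 0.5 SD in either direction is 2 × [1 − Φ(0.5/0.408)] = 0.22. This takes stratification as doing nothing for balance on MHI-5.

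Given an imbalance, the unadjusted follow-up difference is expected to move by *r* times that imbalance. For an imbalance of 0.41 SD the shift is 0.12 SD at *r* = 0.3, 0.20 at 0.5 and 0.29 at 0.7. For 0.5 SD at *r* = 0.6 it is 0.5 × 0.6 = 0.30 SD.

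**Interval widths.**

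- Unadjusted follow-up scores: standard error 0.408; 95% half-width 2.074 × 0.408 = 0.85 SD (22 df).
- ANCOVA on baseline only, relative width: √[(1 − r²)(1 + 1/20)] × t₂₁/t₂₂. At *r* = 0.5: √(0.75 × 1.05) × 2.080/2.074 = 0.89.
- ANCOVA on baseline plus two terms that predict nothing: √[(1 − r²)(1 + 3/18)] × t₁₉/t₂₂. At *r* = 0.5: √(0.75 × 1.167) × 2.093/2.074 = 0.94.
- Two-sample test on change scores: √[2(1 − r)].

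| Assumed *r* | ANCOVA, baseline only: relative width | Half-width (SD) | ANCOVA, two further non-predictive terms: relative width | Change score: relative width |
|---|---|---|---|---|
| 0.3 | 0.98 | 0.83 | 1.04 | 1.18 |
| 0.4 | 0.94 | 0.80 | 1.00 | 1.10 |
| 0.5 | 0.89 | 0.75 | 0.94 | 1.00 |
| 0.6 | 0.82 | 0.70 | 0.87 | 0.89 |
| 0.7 | 0.73 | 0.62 | 0.78 | 0.77 |

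At *r* = 0 baseline-only ANCOVA is slightly worse than no adjustment (half-width 0.87 against 0.85). Simulation of 20,000 trials at each of three correlations agrees with the formula. The standard errors, unadjusted against ANCOVA, are 0.409 and 0.399 (*r* = 0.3), 0.407 and 0.362 (0.5), and 0.408 and 0.298 (0.7).

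**Scores against changes.** Dividing the same raw difference by the SD of change instead of the SD of scores multiplies the standardised effect by 1/√[2(1 − r)]: 0.85 at *r* = 0.3, 1.00 at 0.5 and 1.29 at 0.7.

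**Why the correlation is worth reporting.** For an assumed effect of 0.5 SD, 80% power and two-sided 5%, the unadjusted main trial needs 2 × (1.960 + 0.842)²/0.5² = 62.8, so 63 per arm. Multiplying 62.8 by (1 − r²) gives 48 at *r* = 0.5 and 33 at *r* = 0.7.

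**Stratifiers.** Gender by five levels of support-group use makes up to 10 cells, or 24/10 = 2.4 people per cell. Arm, baseline and all cells leave 24 − 1 − 1 − 10 = 12 residual df. Gender and support-group use as single terms leave 24 − 5 = 19.

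**The case against.** This is a feasibility study, expressly not powered, and its continuation criteria rest on feasibility and acceptability. The only downstream use of the effect size is as an initial estimate. At *r* = 0.5 the half-width is 0.75 SD adjusted against 0.85 unadjusted, and both are too wide to fix a main-trial effect. The gain also depends on a correlation nobody has stated. All of this stands, and it limits the weight of the point. It does not remove the case for a change in wording that uses data already in hand.

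It can also be said that the Statistical analysis section, read with the Design section, allows t tests on change, so baseline may not be wholly ignored. That is fair. But a change score is less precise than the plain follow-up score when *r* is below 0.5, and less precise than baseline-only ANCOVA throughout the table.

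Three stronger readings are tempting, and the documents do not support them:

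- **That the sections target different estimands.** Under randomisation expected baselines are equal, so change and follow-up scores estimate the same mean difference. The estimator, its variance and the scale of a standardised effect differ.
- **That the unadjusted result is biased or its interval invalid.** Chance imbalance is random error, and the unadjusted interval already allows for it.
- **That leaving out the stratifiers makes the standard errors wrong in a way that matters here.** Nothing in the documents gives a size. Omitting prognostic stratifiers usually makes the unadjusted standard error too large, which is conservative.

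**Conclusion.** The point holds as a modest, inexpensive improvement. The protocol article names the tests, so this is a choice fixed in the text and not a detail left to an unseen analysis plan. No between-group analysis adjusts for the baseline value, and the Abstract and Design sections disagree on the quantity compared.

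The cost is avoidable noise. If *r* lies between 0.5 and 0.7, baseline-only ANCOVA narrows the interval by about 11% to 27%; with two further terms that predict nothing, the narrowing is about 6% to 22%. At *r* = 0.4 the gain is about 6% with baseline alone and nil with the extra terms. At about 0.3 or lower it is negligible or slightly negative. These figures assume 12 analysed per arm and equal SDs at the two times. The inconsistency between scores and changes needs reconciling whatever the correlation proves to be.

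**What to change.** For MHI-5 as primary outcome measure, and for the other scales where feasible, estimate the arm difference at weeks 8 and 14 by ANCOVA of the follow-up score on arm and the baseline score of the same scale. Report the adjusted mean difference with its 95% confidence interval, the SD of scores and the baseline/follow-up correlation. Base any standardised effect on the SD of scores. Keep a rank-based analysis as a sensitivity analysis for clearly non-normal scales.

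Stratifiers may be added sparingly, gender and support-group use each as a single term. With 24 people, baseline alone is the safer default, and the choice should be stated in advance. Amend the Abstract, Design and Statistical analysis sections so that all three name the same quantity.

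The change is to wording only and needs no new data. It costs one degree of freedom of 22 for baseline alone, or three with both stratifiers, and brings little or no gain if baseline turns out to predict follow-up poorly.

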### Control group

Participants allocated to the control group will be asked to continue with their normal day to day life as usual. Measures will be taken again post-intervention period (week 8) and 6 weeks post intervention (week 14) to describe potential preliminary differences between the control and intervention group. After the study period, an information pack including useful information and activities that were part of SOLACE will be provided to this group.

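### The effect size meant to inform the main-trial sample size is named Cohen's α, which is not an effect size; if Cohen's d is meant, it is about 3.6% too large on average at 12 per arm

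*Protocol article*

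**What the plan says.** The Statistical analysis section of the protocol article states: "Standard effect sizes of the primary outcome measure will be calculated". The same sentence gives the name of the measure, "will be calculated (Cohen’s *α*) with confidence intervals", and its use, "to provide an initial estimate for sample size calculation for a future main RCT".

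Earlier in that section two kinds of contrast are planned: "Within group comparisons of the outcomes, measures will be made as well as between groups comparisons to examine preliminary effectiveness". The within-arm tests are specified as follows: "To assess potential within-group differences, dependent *T* tests (for normal distribution) or Wilcoxon signed-rank tests".

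The Sample size section sets 24 participants, 12 per group. The Control group section gives two follow-up assessments, at weeks 8 and 14. The effect-size sentence does not mention a small-sample correction.

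**The concern.** The printed name is wrong. In the subsections on public stigma, courtesy stigma and self-compassion, α is an internal-consistency coefficient. It is not a standardised difference, and no passage says what was meant. The error sits in the operative analysis text and concerns a number with a stated use after this trial.

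Reading it as Cohen's d restores a usable measure, but d is biased upward in small samples. Required sample size varies as one over the square of the effect size, so an overstated d makes the next trial too small. What is at stake is a modest, avoidable loss of power in that trial. The feasibility aims of this study are not affected.

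**Working it through.** **Is there a figure to reproduce?** No. The target of 24 is not derived from an effect size, and no main-trial size is given.

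**Inputs.** From the article: 12 per arm, equal allocation, and follow-up at weeks 8 and 14. Assumed, because the article does not give them: a true between-arm d of 0.5 (0.3 and 0.8 as the range), a two-sided 5% test, main-trial power of 80% (90% as a check), and SD = 1.

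**Step 1: the bias in d.**
- df = 2 × 12 − 2 = 22.
- J = Γ(df/2) / [√(df/2) × Γ((df−1)/2)] = Γ(11) / [√11 × Γ(10.5)] = 0.9655.
- The average uncorrected d is the true d divided by J, and 1/0.9655 = 1.036. So d is 3.6% too large on average.
- If fewer complete follow-up (assumed; the article gives no drop-out rate), the excess is 4.4% at 10 per arm and 5.0% at 9 per arm.

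**Step 2: the effect on the main trial.** Per-arm n = 2(1.960 + 0.842)² / d² = 15.70 / d².
- True d = 0.5: 15.70 / 0.25 = 62.8, so 63 per arm.
- Average uncorrected d = 0.5 × 1.036 = 0.518: 15.70 / 0.268 = 58.5, so 59 per arm.
- Actual power with 59 per arm: Φ(0.5 × √(59/2) − 1.960) = Φ(0.756) = 77.5%.
- Same calculation at true d = 0.3: 163 instead of 175 per arm, power 77.3%. At 0.8: 23 instead of 25, power 77.4%.
- Planning for 90% power at d = 0.5: 79 instead of 85, power 88.1%.

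**Step 3: the bias beside the sampling error.** For an observed d of 0.5 with 12 per arm, t = 0.5 × √(12/2) = 1.22. Inverting the noncentral t distribution on 22 df gives a 95% interval of −0.32 to 1.31, a width of 1.63. The bias is 0.518 − 0.500 = 0.018, about 1% of that width.

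**Step 4: a paired within-arm value, if one were ever used.** Suppose the raw change is the same in both contrasts, the SD is equal at both times, and the baseline-to-follow-up correlation is r. The paired value is then 1/√(2(1−r)) times the between-arm value, so the implied sample size is multiplied by 2(1−r). The article gives no r, so these values are assumed:

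| r | size ratio 2(1−r) |
|---|---|
| 0.4 | 1.2 (main trial too large) |
| 0.5 | 1.0 (no distortion) |
| 0.6 | 0.8 |
| 0.7 | 0.6 |
| 0.8 | 0.4 |

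Control-arm change matters as well. With a true between-arm d of 0.5 and r = 0.5, an assumed control improvement of 0.2 SD makes the within-arm value 0.7 and the implied size 33 per arm. A control worsening of 0.2 SD makes it 0.3 and the size 175 per arm. Neither the size nor the direction of the distortion can be read from the article.

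**The case against.** The strongest reply is that this is a one-character slip. Anyone sizing a trial will read d, confidence intervals are planned, and the value is presented only as a first estimate. A 3.6% bias is negligible beside an interval 1.63 wide. The article is also condensed, so the standardiser and the small-sample correction may be set out in a document not shown.

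Most of this stands. The slip is easy to recognise, the bias is small, and silence on the standardiser or the contrast is not an error in itself. But the name as printed is wrong and uncorrected, and the measure it most plausibly stands for has a bias of known direction that costs nothing to remove.

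A reader might infer more: because within-arm tests are planned alongside and the sentence speaks of effect sizes in the plural, a paired value could be carried forward and shrink the main trial by 40%. The documents do not support this. The stated use is to size a randomised trial, and the Design section describes a parallel comparison against controls. Both point to a between-arm value. The two follow-up times are enough to explain the plural. The 40% figure needs an assumed r of 0.7; the distortion vanishes at r = 0.5 and reverses below it.

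**Conclusion.** The point holds in a limited form. The named statistic is not an effect size, and the likely intended one is biased upward by about 3.6% at full recruitment and retention. For an assumed true d of 0.5 and 80% planned power, that means 4 fewer participants per arm and 2.5 points less power; the power loss is similar at 0.3 and 0.8. These figures describe the average d. Any single estimate from 24 people will vary far more than this, and correcting the bias does not make the resulting sample size precise.

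The choice between within-arm and between-arm values needs only a clarifying clause and is not a demonstrated fault.

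**What to change.** Replace the effect-size sentence with wording such as:

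> Hedges' g for the between-arm MHI-5 difference, standardised by the pooled SD, with a 95% confidence interval, reported at each follow-up (weeks 8 and 14) with the raw mean difference and SD. Within-arm effect sizes are descriptive and are not used for sample size.

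This needs no new data or procedures. Giving the raw difference and SD lets the main-trial team see the components of the standardised value. The one downside is a slightly less favourable figure: at 12 per arm, an observed d of 0.50 would be reported as g = 0.50 × 0.9655 = 0.48.

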### Data monitoring and management

All study data will be captured electronically in a secured online survey platform (www.qualtrics.com). The data will then be uploaded into the IBM SPSS database. Qualitative data will be collected using audio recordings, written notes and memos. The program Nvivo will be used to analyse the qualitative data. Recordings of the online intervention will be securely stored on the researcher’s password protected laptop and only used to assess fidelity to the intervention manual during meetings with the research team. All data will be anonymised and electronically stored at the University of Bedfordshire, separate from identifying information. Access to data will be password-protected. Only the research team will have access to the final dataset. All collected data will be used only for the purposes of this research.

### Ethical considerations

This study is being conducted in accordance with the ethical guidelines of the Institute of Health Research to ensure trial integrity as well as participants’ safety and well-being. Ethical approval was granted on January 1, 2018 (ref: IHREC812), from the University of Bedfordshire, Institute of Health Research’s ethics committee.

Respondents who are interested in taking part will receive detailed information about the study and have the opportunity to ask questions. Digital informed consent will be obtained from all participants before the start of the study. Participants are allowed to withdraw from the study at any time and it will be made clear that their anonymity will be respected at all times in the dissemination of results.

### Harms

The intervention is considered safe and there is no evidence to suggest that the planned intervention will be reasonably likely to cause any harm to participants. It is anticipated that the benefits of the study will be greater than any possible risk. Participants will be told that in the event that they do feel distress, they can withdraw from the study at any time. In such cases, we will offer participants the opportunity to debrief with the facilitator, as well as a list of caregiver mental health resources (including services across the county and relevant online support groups). Likewise, it is unlikely that participants will experience any harm during the focus group interview given that the focus will primarily regard the feasibility, practicality and acceptability of the intervention. It is ensured that all questions and probes used are phrased sensitively. Any adverse events that do occur will be recorded and reported when necessary. A protocol and record log for adverse events will be utilised.

## Discussion

The study described here aims to determine the feasibility and preliminary impact of an 8-week psycho-social stigma support intervention, ‘SOLACE’, with a group of parents and carers of newly diagnosed autistic children. To our knowledge, this study will be the first RCT to evaluate the feasibility and preliminary effects of a stigma support intervention for parents/carers of autistic children. As previously highlighted, parents/carers of autistic children are particularly vulnerable to poor mental health and well-being, and the stigma of autism likely significantly contributes to this. Therefore, an intervention that is evidenced to improve psychological well-being in part through increasing resistance to stigma will be of substantial benefit to families and, ultimately, their children. This study represents the first step towards achieving this goal. The learning generated from this study will enable the preparation for a future larger trial that can more confidently assess SOLACE’s effectiveness in improving psychological well-being.

The strength of the study design is the inclusion of a qualitative analysis to assess the feasibility of the intervention. Further, this feasibility study will provide a reliable indication of the sample size needed for an RCT testing the effectiveness of the intervention. It will also address a large gap in the autism-stigma literature since not much is known yet about the path between stigma and psychological well-being. However, as usual with feasibility studies, only preliminary conclusions on the effectiveness of the intervention can be drawn, owing to the small sample size.

The carer population is known to experience many barriers to attendance. SOLACE aims to overcome this barrier by delivering a combination of face to face and online sessions. This should also mean it is relatively easy to implement and to replicate in the future. If SOLACE is feasible and eventually proven to be effective, then health and social care services can commission and include the intervention as part of their service provision. The evidence may also be used to help shape future local and national (and potentially international) autism policy so that the importance of stigma in relation to caregivers’ psychological well-being and their caregiving role is emphasised.

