### Sample size

As this is a feasibility study, it is not powered to determine statistical significance. The target recruitment for this feasibility trial is 24 (12 per group). This number is deemed appropriate for the study aims and consistent with recommendations for behavioural group intervention with this population [32].

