### Outcome measures

Continuation criteria will be used to assess if further evaluation of this intervention is justified, through a formal RCT. The criteria for continuation will be based around feasibility and acceptability. A mix of quantitative and qualitative evaluation processes will be used to evaluate the feasibility of the intervention.

The outcome measures to assess feasibility and acceptability are the following:Recruitment rate, including willingness to be randomised.Drop-out rates including reasons will be recorded to help determine the acceptability of the intervention to participants.Missing data will be descriptively analysed in order to evaluate the acceptability of the data collection measures and procedures.Incidence of adverse events will be recorded that may arise during the intervention period.To evaluate the acceptability of SOLACE and the outcome measures, participants from the intervention group will be invited for a qualitative focus group discussion in week 9. The focus group interview will be audio-recorded for analysis. A topic list will be used to evaluate the intervention content, structure, format and mode of delivery. Positive quality feedback of participants regarding their experience of undertaking SOLACE should indicate whether a larger trial may be feasible.

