### Primary outcome measure

#### Psychological well-being

Psychological well-being will be measured with the validated and reliable 5-item ‘Mental Health Inventory’(MHI-5) [35] . Participants are asked to rate on a six-point scale how often they felt as described during the past month, e.g. ‘During the past month, how much of the time were you a happy person’. The MHI-5, which is used as the measure of common mental disorder, has excellent validity and reliability in measuring symptoms consistent with depression and anxiety [36] and has a long history of use in large-scale health studies [37], including within the caregiver population [36].

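### Twelve participants per arm cannot give the reliable main-trial sample size that the Discussion promises, because the only sizing input described is the pilot effect size on MHI-5

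*Protocol article*

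**What the plan says.** Three places in the protocol article bear on this.

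- **Discussion.** Among the strengths of the design, the article says that "this feasibility study will provide a reliable indication of the sample size needed for an RCT testing the effectiveness of the intervention". Two sentences later it accepts that only preliminary conclusions on effectiveness can be drawn, because the sample is small.
- **Statistical analysis.** Standard effect sizes of the primary outcome are to be calculated "with confidence intervals to provide an initial estimate for sample size calculation for a future main RCT". The measure is printed as Cohen's α and is read here as Cohen's d.
- **Sample size.** The target is 24 participants, 12 per group. The study is described correctly: "it is not powered to determine statistical significance". The number rests on judgement and a cited recommendation ("This number is deemed appropriate for the study aims and consistent with recommendations for behavioural group intervention with this population"), with no precision target for an effect size or an SD.

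The article gives no expected effect, SD or important difference for MHI-5, and it describes no other route to the main-trial sample size.

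**The concern.** The Discussion sentence mentions neither the effect size nor 12 per arm. The link comes from Statistical analysis, which names the effect size as the sizing input, and from Sample size, which fixes the data behind it. Read together, they promise reliability for a quantity that depends on one of the least precise estimates in the pilot. Required sample size varies as 1/d², so error in d is magnified.

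The concession about effectiveness and the claim about sample size also rest on the same MHI-5 contrast. If the effect estimate is only preliminary, a sample size computed from it cannot be reliable.

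What is at stake is the next trial. A team that takes the sentence at face value could run a badly underpowered trial after a chance high estimate. After a chance low one, it could run an oversized trial or abandon the intervention.

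**Working it through.** **Inputs from the article:** 12 per arm (Sample size); a standardised effect size with a confidence interval (Statistical analysis). There is no power calculation behind the 24, so there is no figure to reproduce.

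**Assumptions, because the article gives none:** main trial at two-sided 5% and 80% power; true d of 0.3, 0.5 or 0.8; no drop-out, with 10 or 9 completers per arm as variants; no allowance for clustering from group delivery.

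**Step 1: precision of d.** Near d = 0 the standard error is √(2/n) = √(2/12) = 0.41, so the 95% half-width is 1.96 × 0.41 = 0.80. With 10 completers per arm it is 0.88, and with 9 it is 0.92.

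**Step 2: what that means for the sample size.** The intervals are exact (noncentral t) at 12 per arm. N per arm is from the two-sample t-test; the normal formula 2 × (2.80/d)² gives one fewer at the estimate when d is 0.5 or 0.8.

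| Observed d | 95% CI | N per arm at the estimate | at the upper limit | at the lower limit |
|---|---|---|---|---|
| 0.3 | -0.51 to 1.10 | about 175 | about 14 | none (below zero) |
| 0.5 | -0.32 to 1.31 | 64 | 11 | none (below zero) |
| 0.8 | -0.04 to 1.63 | 26 | about 8 | none (below zero) |

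The interval includes zero in every row.

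**Step 3: direct plug-in of the observed d.** The derived N is 2 × (2.80/d_obs)², so its ratio to the correct N is (d_true/d_obs)².

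- N is within 25% of correct when d_obs lies between d_true/√1.25 = 0.89 d_true and d_true/√0.75 = 1.15 d_true.
- True power in the main trial falls below 50% when d_obs exceeds (2.80/1.96) × d_true = 1.43 d_true.
- No sample size can be derived when d_obs is zero or negative.

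With d_obs following the noncentral t distribution on 22 df:

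| True d | N within 25% of correct | Main-trial power below 50% | d_obs zero or negative |
|---|---|---|---|
| 0.3 | 7% | 38% | 23% |
| 0.5 | 12% | 31% | 11% |
| 0.8 | 19% | 23% | 2.5% |

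Simulation of 400,000 pilots for each true d agrees. At a true d of 0.5, where the normal formula gives 63 per arm, the middle 80% of derived sample sizes among positive estimates runs from 13 to 637 per arm.

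**Step 4: the SD as an alternative input.** The 95% limits for a pooled SD on 22 df are √(22/χ²) at the 97.5% and 2.5% points: 0.77 to 1.42 times the estimate. With a fixed target difference, N varies as SD², so the multiplier is 0.77² = 0.60 to 1.42² = 2.0. This is still imprecise, but it is bounded, unlike an N based on d.

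**The case against.** The strongest defence is that the operative section is more modest than the Discussion. Statistical analysis calls the effect size an initial estimate, plans a confidence interval that would expose the imprecision, and sets no rule for using the point value. A future trial would need its own sample-size justification. This stands. A reader might infer from the Discussion that the main trial will be sized mechanically on the observed d, but the article does not say so. The plug-in rates therefore describe one possible use, not a planned one.

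A reader might also infer that the effect size is the only quantitative result passed to the main trial. The article does not support that. Outcome measures and Statistical analysis also provide for recruitment, willingness to be randomised, drop-out, retention, missing data and standard deviations. What holds is narrower: the effect size is the only input that the article links to the main-trial sample size.

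Nor is it a fault that the pilot is unpowered. That statement is correct and is cited here only as context.

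It is also fair to say that the size of the problem depends on an unknown true effect, that the article gives no important difference for MHI-5, and that the pilot SD is imprecise too. None of this rescues the word reliable: even at a true d of 0.8, about four pilots in five would give a sample size more than 25% off. The caveat in the Discussion concerns effectiveness and leaves the sample-size sentence uncorrected.

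**Conclusion.** The concern holds as an overstatement of what the design can deliver. With 12 per arm, d is known only to about ±0.8 SD, and less well after drop-out. Under direct plug-in at a true d of 0.3 to 0.8, the derived sample size is within 25% of the correct one in about 7% to 19% of pilots. The main trial has under 50% power in about 23% to 38%, and d is zero or negative in about 3% to 23%.

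These figures rest on the assumed significance level, power, true effects and complete follow-up. Drop-out would make them worse, and so, if anything, would clustering. The direction does not depend on any single choice.

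Severity is moderate. No stated number is wrong, nothing in the conduct or analysis of this trial is affected, and the harm depends on how a later team uses the estimate.

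**What to change.** 1. **Discussion:** delete the claim of reliability. State instead that at 12 per arm the 95% interval for d is about ±0.8 SD with no drop-out, and wider with it.
2. **Statistical analysis:** report d with its confidence interval descriptively, and say that the main trial will not be sized on the observed d.
3. **Sizing route:** say that the target difference will come from a justified important difference on MHI-5. That value must be sourced, since the article gives none.
4. **Pilot inputs:** use the pilot for the MHI-5 SD, the baseline/follow-up correlation and attrition, each with its uncertainty. For the SD, the 95% limits are 0.77 to 1.42 times the estimate at 22 df. How conservative a value to carry forward is a matter of convention and should be stated in advance.

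The SDs, retention rates and interval for d are already planned, so the new elements are the wording, the important difference and the correlation. No new data are needed. The cost is a less favourable claim for the pilot.
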